### Measures

All measures will be assessed at baseline and following the 12-week intervention. Measures of cognitive function (primary outcome) and cardiovascular function (secondary outcome) will be conducted in the laboratory by trained research assistants across two lab visits lasting approximately 2 h each. A battery of psychosocial questionnaires will be given to the participant to complete at home along with an Actigraph accelerometer (wGT3X-BT) that participants will be asked to wear for 7 days and nights to record objective levels of physical activity and sleep quality. We will schedule the testing appointments 1 week apart, so participants have time to complete the questionnaire packet and wear the accelerometer before returning to the lab.

#### Cognitive function (primary outcome)

The primary outcome of the trial is cognitive function. Specifically, we will measure executive function, attention and processing speed, memory, and working memory using the tests presented in Table 1. These measures have been used in the exercise-cognition literature and are partly adapted from the NIH Toolbox. The tasks are computer- and paper-based and will be administered over the two testing sessions on separate days and repeated again after the 12-week intervention. The first testing session consists of immediate and delayed word recall [18], flanker task [19], spatial working memory [20, 21], trail making [22], and matrix reasoning [23] task. The second session consists of relational memory [24], pattern comparison [25], and task switching paradigm [14, 21]. All measures involve a practice phase that explains the task instructions and allows participants to familiarize themselves with the test.

**Table 1 Tab1:** Battery of neurocognitive tests administered at baseline and follow-up

Cognitive test	Cognitive domain	Approximate test duration
Word list (immediate and delayed recall)	Short- and long-term memory	5 min
Flanker task	Attention and inhibitory control	8 min
Spatial working memory	Spatial memory	15 min
Trail making A and B	Visual scanning, mental flexibility, processing speed	5 min
Matrices	Fluid intelligence	10 min
Spatial reconstruction task	Relational memory	Self-paced, 20 trials
Pattern comparison	Processing speed	4 min
Task switching	Mental flexibility	15 min

#### Cardiovascular function (secondary outcome)

The secondary outcome of the trial is cardiovascular function. A submaximal treadmill test will be administered at baseline and after the 12-week intervention. We will use a modified Balke protocol [26] that estimates a participant’s predicted VO2max based on the incline, speed, and heart rate over the last two stages completed during the test. The modified Balke is a well-accepted treadmill protocol that keeps the speed constant (3.0 mph) and workload by increasing the incline by 2.5% every 3 min. The test will terminate when the participant reaches 85% of their age-predicted maximum heart rate. We will then use their speed, incline, and heart rate from the last two completed stages, as well as their age-predicted maximum heart rate, to calculate their predicted VO2_max_ [27]. Before the test, anthropometric measurements including height, weight, resting heart rate, and resting blood pressure will be recorded. During the test, blood pressure and a rating of perceived exertion [26] will be recorded every 3 min for participant safety. Test will conclude once participant’s reach their 85% predicted maximum heart rate. In the event of participants taking prescription medications that are beta-blockers, a rating of perceived exertion of 17 will serve as an indicator for test termination. All participants will be led into a 3-min walking cool down at 2.0 mph followed by a 2-min seated rest. Heart rate and blood pressure will be monitored throughout the cool down to ensure participant is back at his/her resting state.

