Yoga is a noteworthy exercise modality that should be examined for its improvements in cognitive function and quality of life in clinical populations. As a holistic, mind-body activity, with components centered on meditation, breathing, and postures, it has shown great potential to improve cognitive function [13, 14]. Moreover, it is a low-impact exercise modality that may be more suitable by people limited in their mobility and function. However, little is known about the potential of yoga in maintaining or enhancing cognitive function and/or reducing CRCI among cancer survivors. An evidence-based review of yoga for cancer patients and survivors [15] reviewed 10 yoga-based interventions and noted some positive results, with outcomes primarily focused on psychosocial health and well-being (quality of life, depression, anxiety and stress being the most common). None of the reviewed interventions addressed cognitive function or CRCI.

STAY Fit is designed as a pilot three-arm randomized controlled trial, comparing the benefits of a 12-week yoga and aerobic walking intervention, using a stretching-toning group as an active control. In line with the purpose of conducting pilot studies, we designed this trial to test the feasibility of our methods and procedures for a future large-scale intervention and to explore possible effects and associations as a function of yoga practice on cognitive health [16]. The primary outcomes are measures of cognitive function, specifically domains of executive function, attention, memory, processing speed, and working memory. Secondary outcomes include cardiovascular fitness changes over the course of the intervention. Tertiary measures will examine changes in self-reported quality of life and psychosocial outcomes. Our protocol has been reported here in accordance with the SPIRIT checklist (see Additional file 1).

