### Subjects

The inclusion criteria are low physical activity engagement (i.e., less than 150 min of moderate to vigorous exercise per week), including no yoga practice over the last 6 months; aged between 30 and 70 years; capable of performing yoga, aerobic walking, or stretching and toning exercise without any pre-existing condition(s), as determined by their personal physician; the type of cancer (i.e., types of brain cancers are excluded as they could confound with cognitive study outcomes); the last treatment for cancer being at least 1 year from the beginning of the exercise program; not planning to receive any cancer-related treatment during the study period; intention to stay in the Champaign-Urbana area over the duration of the study; comfortable with reading, writing, and speaking English; and willingness to be randomized. Finally, all participants will be required to complete the Physical Activity Readiness Questionnaire (PAR-Q [17];) and must obtain approval from their personal physician, if deemed high-risk on the PAR-Q. The physician approval process will be facilitated by the research staff to minimize participant burden.

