#### Aerobic walking intervention arm

Participants randomized to the walking intervention arm will meet three times a week, 60 min a session, for the 12-week intervention. The intensity of each walking session will be individualized for each participant. The 12-week structure of the walking sessions, including the intensity and duration for each week’s sessions, is presented in Table 3. The rating of perceived exertion (RPE) and target heart rate (HR) zones were selected in accordance with the ACSM exercise prescription guidelines for cancer survivors. Within each 4-week block, participants started at the lowest recommend intensity for 15 min, gradually increasing the duration to 40 min with the target HR zone. Prior to the start of the intervention, researchers will calculate each participant’s target HR zones using the Kavonen formula [29] ([(HR_max_ − HR_rest_) × % training intensity] + HR_rest_), where HRmax = 220 − age and HRrest = resting heart rate recorded at baseline submaximal treadmill test. All walking sessions are led by trained exercise leaders, who are trained with the detailed protocol for the sessions, and complete 2-h-long orientations to review the manual of procedures and protocols including participant safety, leading warm up and cool down exercises and adapting the intensity of exercise to target the HR zones. During each session, exercise leaders are responsible for monitoring the participant’s heart rate every 5 min to ensure they stay within their designated heart rate zone. Participants will be allowed to freely change the speed and/or incline during the session to stay in the target HR zone. If needed, participants will be given wrist and/or ankle weights to wear to keep them at a higher intensity. Sessions will begin with a 5-min warm up including dynamic stretching and brief aerobic activity (e.g., marching in place, high knees) and end with a 5-min slow walking cool down and static stretching until the participant HR returns to pre-exercise resting levels.

**Table 3 Tab3:** ACSM’s aerobic exercise prescription for cancer survivors and protocol for the STAY Fit walking group

Weeks	1–4	5–8	9–12
Rating of perceived exertion	12–13	14–15	16–17
Target heart rate zone (% of heart rate reserve)	40–59	60–70	70–89
Duration (minutes)	15–40	15–40	15–40

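### Predicted VO2max cannot be computed for participants who stop before completing two treadmill stages, and mean imputation would give these least fit participants average fitness

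*Protocol article*

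**What the plan says.** The section on cardiovascular function names one outcome: "The secondary outcome of the trial is cardiovascular function". The Background agrees ("Secondary outcomes include cardiovascular fitness changes over the course of the intervention"), and the abstract makes fitness change the second aim.

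The treadmill protocol "keeps the speed constant (3.0 mph) and workload by increasing the incline by 2.5% every 3 min". The starting incline is not given. On stopping: "The test will terminate when the participant reaches 85% of their age-predicted maximum heart rate". For participants on beta-blockers, "a rating of perceived exertion of 17 will serve as an indicator for test termination". The outcome is then calculated as predicted VO2max: "We will then use their speed, incline, and heart rate from the last two completed stages, as well as their age-predicted maximum heart rate". The formula for age-predicted maximum is stated only for the walking arm's training zones ("where HRmax = 220 − age"); I assume that it also applies to the test.

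The trial enrols adults aged 30 to 70 who are not regularly active: "The inclusion criteria are low physical activity engagement (i.e., less than 150 min of moderate to vigorous exercise per week". The Statistical analysis section states that missing data will be filled by mean imputation. It makes no exception for an outcome that is missing because it could not be calculated.

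**The concern.** The calculation needs two completed stages, but the stopping rule does not guarantee them. A participant whose heart rate reaches the stop during the first or second stage has taken the test exactly as planned and still has no predicted VO2max. That outcome is determined by low fitness, so the values are missing because of the quantity being measured.

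Filling such a gap with the mean of the participants who do have a value is wrong in a known direction: it overstates fitness. The damage to change scores can be worse. A participant who trains successfully may complete two stages at follow-up but not at baseline. An imputed average baseline followed by a low but real follow-up value then records a decline where there was a gain. This should happen most in whichever arm improves fitness most, so it works against the comparison that Aim 2 is meant to inform.

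**Working it through.** The documents state no figure for the share without a value or for the precision of predicted VO2max, so there is none to reproduce. The sample size of 75 concerns cognition and does not bear on this point.

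**Inputs from the protocol article:** 3.0 mph; +2.5% incline per 3-minute stage; stop at 85% of age-predicted maximum; maximum = 220 − age; ages 30 to 70; 75 participants, 25 per arm.

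**Assumptions not in the documents:** standard walking oxygen cost; heart rate linear in oxygen uptake; resting heart rate 72 (SD 9 in simulation); true maximum heart rate with SD 10 around 220 − age; true VO2max with SD 5.

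**Step 1. Cost of each stage.** 3.0 mph is 80.4 m/min. VO2 = 3.5 + 0.1 × 80.4 + 1.8 × 80.4 × incline. This gives 11.5 at 0%, 15.2 at 2.5% and 18.8 at 5% (mL/kg/min).

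**Step 2. Fitness needed to complete two stages.** Let f be the fraction of heart-rate reserve available at the stop:

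f = (0.85 × HRmax − HRrest) / (HRmax − HRrest)

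Threshold VO2max = 3.5 + (stage-2 VO2 − 3.5) / f

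- Age 70: HRmax = 150, stop = 127.5, f = 55.5 / 78 = 0.712. With a 0% start: 3.5 + 11.66 / 0.712 = 19.9.
- Age 50: HRmax = 170, stop = 144.5, f = 72.5 / 98 = 0.740. With a 0% start: 3.5 + 11.66 / 0.740 = 19.3.
- Ages 30 to 70 and resting rates 60 to 90: 18.4 to 22.2 with a 0% start, 23.1 to 27.9 with a 2.5% start.

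**Step 3. Share below the threshold.** Using 19.9 and SD 5, the share is Φ((19.9 − mean) / 5). Simulation, which also varies age, resting rate and true maximum, gives similar figures:

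| Assumed mean VO2max | Φ formula, 0% start | Simulated, ages 45–70, 0% start | Simulated, ages 45–70, 2.5% start |
|---|---|---|---|
| 22 | Φ(−0.42) = 34% | 33% | 67% |
| 25 | Φ(−1.02) = 15% | 16–17% | 47% |
| 28 | Φ(−1.62) = 5% | 6% | 28% |

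Over the full enrolled age range, 30 to 70, with a 0% start, the shares are about 45% at mean 20, 25% at 23, 11% at 26 and 3% at 30. For the 6% to 33% range, 0.06 × 75 = 4.5 and 0.33 × 75 = 24.75, so about 5 to 25 participants.

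**Step 4. Who they are.** At an overall mean of 23 (ages 30 to 70), those without a value have a true mean of about 17 and those with a value about 25. Imputing the latter mean overstates their fitness by 25 − 17 = 8 mL/kg/min.

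**Step 5. Effect on change.** After an assumed true gain of 10%, about 3% to 12% of participants (0% start) have a follow-up value but no baseline. For illustration, take a 70-year-old with true VO2max 19, below the 19.9 threshold. A 10% gain gives 20.9, above it. With the baseline imputed at 25, the recorded change is 20.9 − 25 = −4.1. The true change is +1.9.

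**Step 6. Is another measure clearly more sensitive?** Median response to a 10% gain, divided by the spread of change when nothing changes (ages 45 to 70, mean VO2max 22 to 28):

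- Stage error 2–3 bpm and day-to-day shift 3 bpm: predicted VO2max 0.50–0.89; heart rate at the highest stage completed at both visits 0.98–1.20.
- Stage error 1 bpm and shift 4 bpm: predicted VO2max about 1.2–1.35; matched-stage heart rate about 1.05.

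The ranking reverses with the error structure. Time to the 85% stop led in all 20 scenarios of one set, but by as little as 1.41 to 1.33. When still more of the error is a shared day-to-day shift, predicted VO2max draws level or moves ahead.

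**The case against.** The article cites sources for the treadmill protocol and the calculation and refers to a manual of procedures. The starting incline, the use of a part-completed stage and the handling of a short test may be settled there, and their absence from an article is not an error. That stands. But the point rests on two rules that the article does state, the two-stage calculation and mean imputation. Applied together as written, they give a wrong value to an identifiable group.

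The affected share is assumed throughout. Activity below 150 minutes a week does not establish a mean VO2max of 22, and participants must be capable of aerobic walking. That also stands: at a mean of 30 the share is only about 3%.

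Randomization is limited to people who complete all baseline measurements. A test ended at its planned stop is most naturally a completed one, so this does not remove the group. If it were read as requiring a computed value, the trial would instead exclude its least fit candidates.

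The Discussion concedes that a submaximal test was chosen for lack of resources, and the pilot is mainly descriptive. Both are true, but the concession does not cover values that cannot be computed, and imputed values distort descriptive means and Cohen's d as well.

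A reader might go further and infer that predicted VO2max is too noisy to use and should give way to heart rate at a fixed stage. The documents do not support this. They give no heart-rate error figure, and the SD of change with no true change runs from 1.5 to 11 mL/kg/min across assumed error structures. Matched-stage heart rate is also undefined for anyone who completes no stage.

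**Conclusion.** The concern holds in a limited form. It follows from the text alone that the outcome is undefined for participants who stop before completing two stages, that the rule selects the least fit, and that mean imputation as stated would credit them with average fitness. The size is conditional: about 6% to 33% without a baseline value at mean VO2max 28 to 22 with a 0% start, more with a 2.5% start, and about 3% if the participants are fitter (mean 30). The bias per affected person is large, about 8 mL/kg/min in the worked case, against a 10% gain of only 2 to 3. Whether predicted VO2max is less sensitive than other measures from the same test cannot be decided from the documents, so this is no ground for replacing it.

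**What to change.** Keep predicted VO2max as the secondary outcome and add the following to the outcome definition and the missing-data rule:

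- Values that cannot be computed for want of two completed stages are not mean-imputed. Their number is reported per arm and visit, including participants with a value at one visit only.
- A companion measure is prespecified that does not need two completed stages: time or workload reached at the 85% heart-rate stop. Its recording should be stated, because the article does not say that test time is kept.
- Beta-blocker users are reported separately. Their test ends on perceived exertion, so the companion measure does not have the same meaning for them.
- Heart rate at the highest stage completed at both visits may be reported as supportive, not as a replacement.

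The test and its stopping rules are unchanged, and no extra visit or equipment is needed. The cost is a wording change and one more fitness measure to record and report.

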**Methods:**

This pilot study aims to recruit 75 adult cancer survivors who will complete assessments of cognitive function, cardiovascular fitness, physical activity, and psychosocial measures at baseline and after the 12-week intervention. The aims of STAY Fit are (1) to assess the efficacy of yoga to improve cognitive function among cancer survivors, compared to aerobic exercise and an active control group; (2) to examine changes in cardiovascular fitness as a result of the interventions; and (3) to assess changes in quality of life among our population as a result of the exercise interventions.

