### Randomization

Participants who are eligible for the study and complete all baseline measurements will be randomly assigned to 1 of the 3 intervention arms using a computer-generated program. Randomization will take place in groups following rounds of advertising and is stratified based on sex, age, and years since cancer diagnosis. Couples or friends who sign up for the study together will be randomized together to avoid contamination across groups. Randomization will take place following completion of all baseline assessments and a week before the 12-week exercise sessions are scheduled to begin. Participants will be notified via a mailed letter and follow-up phone calls confirming their randomized group and logistics (parking and directions) for their 12-week exercise sessions. This is an open label trial with no blinding of participants or assessors.

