### Statistical analysis

Data will be analyzed using SPSS 24.0 (IBM Corp., Armonk, NY). Each of the cognitive domains assessed will be analyzed separately. From each of the assessments administered, latent variables will be created to represent a global cognitive score for each domain. These variables will be created for both baseline and post-intervention test scores. Given the pilot nature of this study, we will focus on descriptive statistics and calculating effect sizes (Cohen’s d values). Data characteristics permitting (normality, multi-collinearity, sample size), we may conduct additional secondary analyses. For example, a time (baseline, follow up) × group (yoga, aerobic, stretching-toning) repeated measures analyses of covariance controlling for relevant covariates (possible covariates include age, education, stage of cancer, months since diagnosis, attendance, and baseline performance) can be employed to explore intervention effects for each of the cognitive domains. Similar repeated measures analyses could examine intervention effects for cardiovascular fitness and the tertiary psychosocial outcomes. Given that this is a pilot study, no additional subgroup or adjusted analyses are planned. An intent-to-treat analysis approach will be used for any dropouts who completed at least one exercise session. Missing data will be handled using a mean imputation approach. Participants’ exercise session attendance and physical activity performed outside of the session (as reported in home logs) will be factored into analyses as appropriate to control for participants’ adherence to study protocols.

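### Beta-blocker users get their own stopping rule but no separate VO2max calculation, so the printed method overstates their predicted VO2max

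*Protocol article*

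**What the plan says.** The Protocol article, section Cardiovascular function (secondary outcome), describes a submaximal modified Balke treadmill test at baseline and after 12 weeks. The test normally stops at 85% of age-predicted maximum heart rate. The outcome is defined twice, each time without an exception. First it is "predicted VO2max based on the incline, speed, and heart rate over the last two stages completed during the test". Then the inputs are given as speed, incline and "heart rate from the last two completed stages, as well as their age-predicted maximum heart rate".

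The one provision for beta-blockers concerns when the test ends: "In the event of participants taking prescription medications that are beta-blockers, a rating of perceived exertion of 17 will serve as an indicator". Perceived exertion is collected in everyone; together with blood pressure it "will be recorded every 3 min for participant safety".

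The eligibility criteria (Subjects) do not exclude beta-blocker users. Statistical analysis does not name the drug among its possible covariates. Aim 2 in the Abstract is "to examine changes in cardiovascular fitness as a result of the interventions", and for reporting the plan says "we will focus on descriptive statistics and calculating effect sizes", namely Cohen's d.

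**The concern.** A separate stopping rule makes sense only if age-predicted heart rate is a poor guide to effort in these participants. The calculation that follows nevertheless uses age-predicted maximum heart rate as the end point of the extrapolation. A beta-blocker lowers exercise and peak heart rate. Carrying the heart rate–VO2 line up to a heart rate the person cannot reach therefore goes past the true peak, and the prediction is too high.

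Three consequences follow:

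- Users' absolute predicted VO2max is wrong.
- With stable use, their change scores are multiplied by a factor above 1.
- If a participant starts or stops the drug between visits, the change score shows a gain or loss that did not happen.

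The third matters most in small arms whose main output is a descriptive effect size.

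**Working it through.** The plan states no figure on this point, so there is none to reproduce.

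**Inputs from the article.** Extrapolation from the last two completed stages to age-predicted maximum heart rate (Cardiovascular function). Maximum heart rate = 220 − age, which is stated for the walking prescription and assumed here for the test. Arms of 25 (Sample size calculation).

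**Assumed inputs.** The cited VO2max equation is not shown and the documents give no beta-blocker data. I assume heart rate linear in VO2; age 60 (age-predicted maximum 160); resting heart rate 60 on the drug; resting VO2 3.5 and true VO2max 25 mL/kg/min, unchanged by the drug; true peak heart rate lowered by L = 10, 15, 25 or 35 bpm; true gain 2.0; SD of change 3.0. Cohen's d is taken as mean change divided by SD of change, so its true value is 2.0/3.0 = 0.67.

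**Formulas.**

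1. Stretch factor: f = (160 − 60)/(160 − L − 60).
2. Predicted VO2max = 3.5 + (25 − 3.5)·f. Extrapolating from two submaximal stages gives the same value, because the line is the same.
3. Stable use: a true gain of 2.0 reads 2.0·f.
4. One participant stops: baseline is inflated and follow-up is not, so the false loss is D = 21.5·(f − 1). Arm mean = 2.0 − D/25; SD = √(9 + 0.04·0.96·D²).
5. One participant starts: follow-up (true value 27) is inflated, so the false gain is D = 23.5·(f − 1). Arm mean = 2.0 + D/25; same SD formula.

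| Peak heart rate lowered by (bpm) | 10 | 15 | 25 | 35 |
|---|---|---|---|---|
| f | 1.111 | 1.176 | 1.333 | 1.538 |
| Predicted VO2max (true 25) | 27.4 | 28.8 | 32.2 | 36.6 |
| Overstatement | 10% | 15% | 29% | 46% |
| Stable user, true gain 2.0 reads | 2.22 | 2.35 | 2.67 | 3.08 |
| One stopper: false loss | 2.4 | 3.8 | 7.2 | 11.6 |
| – arm mean falls by | 0.10 | 0.15 | 0.29 | 0.46 |
| – d (true 0.67) | 0.63 | 0.60 | 0.52 | 0.41 |
| One starter: false gain | 2.61 | 4.15 | 7.83 | 12.65 |
| – arm mean rises by | 0.10 | 0.17 | 0.31 | 0.51 |
| – d (true 0.67) | 0.69 | 0.70 | 0.69 | 0.64 |

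**Sensitivity to the assumptions.** With resting heart rate 55–70 and true VO2max 20–35, the overstatement runs from +9% (resting 55, VO2max 20, L = 10: f = 105/95, predicted 21.7) to +57% (resting 70, VO2max 35, L = 35: f = 90/55, predicted 55.0).

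**Stable users at arm level.** With n users, the mean gain moves by (n/25)·2.0·(f − 1): 0.01–0.04 for 1 user, 0.03–0.13 for 3, and 0.04–0.22 for 5. For d with 3 users (share 0.12), mean m = 2.0·(0.88 + 0.12f) and variance = (0.88 + 0.12f²)·13 − m², where 13 = 3.0² + 2.0². This gives d = 0.67, 0.67, 0.66 and 0.65.

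**Second model.** This one simulates the treadmill stages with a standard walking equation (also an assumption), off-drug resting heart rate 72 and true VO2max 28 at age 60. If peak heart rate falls by 10/20/30% and resting heart rate by 10/15/20%, the prediction is 32.9/39.7/49.6 (+18/+42/+77%). Over ages 50–70 and VO2max 24–32 the range is about +17% to +85%. If the drug only shifts heart rate down in parallel by 10/20/30 bpm, the overstatement is 2.8/5.6/8.4 (+10/+20/+30%). In the proportional scenarios the result did not depend on whether RPE 17 came at 75% or 85% of VO2 reserve. Extrapolating to the person's own drug-limited peak returned the true 28.0, as did the printed method without the drug.

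**The case against.** The strongest reply is that this is an omission from a condensed article. The text does not say outright that the formula is applied to users, and Data Availability refers to a manual of procedures that may score them differently. That uncertainty remains, which is why the point is put as the result of applying the rule as written. It does not remove the point: the article prints the stopping rule, the exception, the inputs and the extrapolation end point, and that rule is wrong for a group it names.

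Other objections carry weight:

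- The number of users is unknown and could be very small or zero. Physician screening under Subjects may reduce it further.
- The covariate list is open and the repeated-measures model optional, so no fixed analysis wrongly leaves the drug out.
- With stable use d barely moves. The largest shift needs someone to stop the drug within 12 weeks and a 35 bpm effect, and nothing in the article suggests that stopping is expected.
- The d used here is a within-arm standardized change; the plan does not define its d. A shift in one arm's mean does pass unchanged into a between-arm difference in mean gain.
- The Discussion already concedes that the submaximal test only estimates fitness, though it does not mention beta-blockers.
- Staff must know who takes a beta-blocker to apply RPE 17, so part of the data capture is implied. Using that information in scoring or reporting is not.

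These limit the consequence. None changes the direction of the error.

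**Conclusion.** The concern holds. The upward direction follows from the printed rule and one outside premise, that beta-blockers lower exercise and peak heart rate, which the separate stopping rule itself implies. The size rests entirely on assumptions: from about +9% to +57% in the main model, and up to +85% in the second.

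The reach is narrow. Stable users distort their own absolute values but hardly affect arm-level results. The material risk to Aim 2 is a change of medication between visits, where one person can visibly move the result of a 25-person arm. The primary cognitive outcome is untouched. The point should be corrected because the remedy is cheap and the pilot is meant to inform a larger trial. Confidence is medium, because the number of users and the full manual are not available.

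**What to change.** 1. Record beta-blocker use at both testing visits.
2. Keep users, like all other randomized participants, in the main fitness analysis, so that no medication-based exclusion cuts across the stated approach: "An intent-to-treat analysis approach will be used for any dropouts who completed at least one exercise session".
3. Add a sensitivity analysis restricted to participants not on a beta-blocker at baseline. The plan says "Randomization will take place following completion of all baseline assessments", so this flag is fixed before allocation and adds no post-randomization selection.
4. Report by arm how many participants start or stop the drug between visits.
5. For users, report by arm the stage or time reached at RPE 17 at both visits, and flag their heart-rate-based predicted VO2max as not valid in absolute terms.

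The cost is one medication field per visit and a few lines of analysis text. No new testing is needed, since perceived exertion is already recorded during the test. The sensitivity analysis has slightly fewer participants and still includes anyone who starts the drug after randomization, hence the counts in step 4. Perceived exertion is subjective and the trial is open label, so the users' stage or time result should be treated as descriptive only.
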